### Research aim and objectives

This study aims to evaluate the combined effect and clinical significance of a multi-strain probiotic intervention (VSL#3®^,^ containing one strain of *Streptococcus thermophilus*, three strains of *Bifidobacterium* and four strains of *Lactobacillus*) provided together with dietary anthocyanins extracted from New Zealand-grown blackcurrants on the gut microbiota profile and inflammatory biomarkers in adults with UC.

We hypothesise that (1) anthocyanins, in combination with probiotics, will result in a reduction in gut inflammation measured by faecal calprotectin (FCAL) and will modulate the gut microbiome measured through shotgun metagenomic sequencing of faecal samples; (2) anthocyanins, in combination with probiotics, will result in a synergistic effect that results in a significantly greater reduction in FCAL and improvement in the gut microbiome than each intervention alone; (3) the reduction in FCAL will be explained by beneficial changes to the gut microbiome profile; and (4) these changes in FCAL and the gut microbiome will lead to clinically significant improvements in health-related quality-of-life measured with the IBDQ-32.

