#### Faecal calprotectin

FCAL will be measured at baseline and 12 weeks. FCAL is a sensitive marker of intestinal inflammation and has been shown to correlate to histological and endoscopic inflammation and disease activity measures.^(54,55)^

Faecal samples for FCAL will be collected in an ELISA kit (Epitope Diagnostic) and stored at −80 °C until all samples are collected. FCAL will be determined with a range of 0–321 μg/g or 0–892 ng/ml calprotectin. The analytical sensitivity (LLOD) of the human calprotectin ELISA as determined by the 95 % confidence limit on 12 duplicate determination of zero standard is approximately 2⋅5 ng/ml. A LLOQ was determined by dilution of assay standards and it is approximately 5 ng/ml.

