### Statistical analysis

Statistical analyses will be performed in Stata software,^(65)^ R software^(66)^ and/or IBM SPSS Statistics.^(67)^ An ITT analysis will be the primary analysis, including all participants randomised and analysed according to the treatment group to which they were originally assigned. A per-protocol analysis will additionally be conducted for all outcomes and used as a sensitivity analysis compared to the ITT. The per-protocol analysis will include participants who completed the trial without major violation including medical disruptions or unblinding, and who exhibited >80 % compliance to the intervention products.

Baseline demographics and measurements will be reported for each intervention group as means and standard deviations or 95 % CI.

The primary outcome will be the mean IBDQ-32 score at week 12 adjusted for baseline and covariates and assessed using an ANCOVA. A sensitivity analysis of differences in within-group change in IBDQ-32 score from baseline to week 12 will be measured using a two-sample *t*-test or Mann–Whitney *U*-test depending on normality of distribution. Within-group differences in secondary outcomes measured at two timepoints will be evaluated using a two-sample *t*-test or Mann–Whitney *U*-test depending on normality of distribution. Within-group differences in secondary outcomes measured at three time points will be evaluated using linear mixed modelling. Between-group differences of outcomes will be explored using ANOVA or ANCOVA if covariates need to be considered or mixed models. Relevant covariates associated with the primary outcome of health-related quality-of- life will be included in the analyses. Secondary analyses will be conducted to investigate relationships between changes in outcome measures. Predictors and assumptions of missing data will be investigated. Methods such as multiple imputation will be considered depending on the data missing. Appropriate sensitivity analyses will be performed.

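### Between-arm tests of faecal calprotectin have no stated scale or normality provision, and baseline adjustment is only conditional; a baseline-adjusted log-scale analysis should be fixed in advance

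*Protocol article*

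**What the plan says.** FCAL is a secondary outcome, but the first two hypotheses are stated in terms of it. Under Research aim and objectives, hypothesis 1 says that the combination "will result in a reduction in gut inflammation measured by faecal calprotectin (FCAL"). Hypothesis 2 says that "anthocyanins, in combination with probiotics, will result in a synergistic effect that results in a significantly greater reduction in FCAL", and sets the comparator as each product alone.

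Under Faecal calprotectin, the timing is: "FCAL will be measured at baseline and 12 weeks". The assay range runs to 321 μg/g (892 ng/ml), and on the lower limit the text says: "A LLOQ was determined by dilution of assay standards and it is approximately 5 ng/ml".

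Under Statistical analysis, three things matter here:

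- The IBDQ-32 sensitivity test, and the tests described as within-group for secondary outcomes at two timepoints, are a t-test or "Mann–Whitney *U*-test depending on normality of distribution".
- Between-arm comparisons have one sentence: "Between-group differences of outcomes will be explored using ANOVA or ANCOVA if covariates need to be considered or mixed models". It names no scale and does not repeat the normality condition. Adjustment applies only if covariates are judged to be needed.
- For the IBDQ-32, by contrast, baseline adjustment is fixed without condition.

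The section closes its provisions with "Appropriate sensitivity analyses will be performed", without further detail.

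**The concern.** The paragraph attends to distribution for some tests and not for those that bear on the FCAL hypotheses. A reduction attributable to the combination, and a greater reduction than with each product alone, are both between-arm statements.

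FCAL is also the outcome where this is most likely to matter. It is a concentration bounded below. Eligibility sets no lower or upper limit on disease activity, so participants in remission and with active disease may both enter. If the distribution is right-skewed, a comparison of raw means is driven by a few high values and loses power. If baseline is left out as well, more is lost.

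The scale also affects what synergy means. Two products that each act proportionally and independently show no interaction on the log scale, but a positive interaction on raw means. If an interaction test is used for hypothesis 2, its result depends on a choice that the published text leaves open.

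**Working it through.** **No figure of the plan to reproduce.** The article gives no SD, effect size or power for FCAL. What follows is a range under stated assumptions.

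**Inputs from the article.** 19 analysed per arm (Sample size and power calculations; derived there for the IBDQ-32 and used here only as the number analysed); α = 0.05, taken as two-sided; FCAL at baseline and week 12; upper limit 321 μg/g = 892 ng/ml; LLOQ about 5 ng/ml.

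**Assay span.** 892/321 = 2.78 ng/ml per μg/g, so the LLOQ is 5/2.78 ≈ 1.8 μg/g. The quantifiable span is 892/5 ≈ 178-fold. This describes the instrument. It shows what the assay can resolve, not how patients are distributed.

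**Assumptions, none from the article.** Log-normal FCAL; baseline/week-12 correlation 0.5 on the log scale; combination halves FCAL against placebo; log-SD 0.8 to 1.6; geometric mean 60 to 300 μg/g.

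**Power by simulation.** Example without a ceiling, geometric mean 60 μg/g. Relative loss = 1 − (raw power / log ANCOVA power).

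| Log-SD | Raw ANOVA | Raw ANCOVA | Log ANCOVA | Loss, raw ANCOVA | Loss, raw ANOVA |
|---|---|---|---|---|---|
| 1.0 | 39% | 45% | 66% | 1 − 45/66 = 32% | 1 − 39/66 = 41% |
| 1.3 | 19% | 23% | 44% | 1 − 23/44 = 48% | 1 − 19/44 = 57% |
| 1.6 | 10% | 12% | 30% | 1 − 12/30 = 60% | 1 − 10/30 = 67% |

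With readings capped at 321 μg/g and log-SD 1.3, raw against log ANCOVA is 33% v 44% at geometric mean 60 (loss 1 − 33/44 = 25%), 37% v 41% at 150 (loss 1 − 37/41 = 10%), and about 37% v 37% at 300 (no loss).

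Over the whole grid (10,000 replicates per cell), the relative loss against log ANCOVA is:

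| | Raw ANCOVA | Raw ANOVA |
|---|---|---|
| No ceiling | 17 to 62% | 26 to 67% |
| Capped at 321 μg/g | −3 to 25% | 9 to 34% |

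The gap between the two columns is the cost of omitting baseline.

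**Scale of synergy.** Let each product independently halve FCAL, with means 100 (placebo), 50, 50 and 25 (combination).

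- Raw interaction: 25 − 50 − 50 + 100 = +25, a positive value that reads as less than additive.
- Log interaction: ln[(25 × 100)/(50 × 50)] = ln 1 = 0.
- Combination against each single product: 25 − 50 = −25 raw and 25/50 = 0.5 as a ratio. Both favour the combination.

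For each-product ratios of 0.5 to 0.7 and log-SD 1.0 to 1.3, capping at 321 μg/g changes the raw interaction to between +1.5 and +19.5 μg/g at medians of 80 to 150, and to between −2.5 and +1.6 μg/g at a median of 300. The log interaction is then −0.01 to −0.14 rather than 0. Neither scale is neutral if capped values are taken at face value.

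**The case against.** The strongest reply is that silence is not a decision. ANOVA, ANCOVA and mixed models can all be run on log values, and the scale for one secondary biomarker is ordinary analysis-plan content. That plan is not shown, and this is a condensed article. This stands: a reader might infer that the protocol commits to untransformed FCAL, and it does not.

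A second reply is that the normality provision may already reach FCAL. The tests labelled within-group are two-sample tests, so a comparison of changes between arms may be meant. That reading is possible. It would leave FCAL with two between-arm methods, and the rank-based one would carry no covariate adjustment for baseline.

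Third, the skewness is assumed. The article reports no FCAL distribution, and the Discussion describes the population as having mild-to-moderate disease. This also stands, and is why the size is given only as a conditional range. A reader might infer that the trial loses a third to two thirds of its power for FCAL. The documents do not support that: such losses need readings without a ceiling and a log-SD of about 1.0 or more, and under the stated assay range the loss is smaller and can vanish.

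Fourth, a reader might infer that a raw-scale analysis would turn independent benefits into antagonism. That presumes an interaction test, and the article states none. Hypothesis 2 asks for a "significantly greater reduction in FCAL and improvement in the gut microbiome than each intervention alone", which reads as pairwise comparisons, and the example above does not reverse these.

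Finally, FCAL is secondary, its comparisons are described as exploratory, and no power is claimed for it, so no stated figure is contradicted.

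**Conclusion.** The point holds in a limited form. The published text names the between-arm methods for FCAL but gives no scale and no clear normality provision for them, and it makes baseline adjustment conditional although baseline FCAL is collected. A better method is available from data already in the schedule.

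The size rests on assumed log-normality, correlation 0.5, a true halving and 19 per arm, and it turns on whether high samples are read beyond 321 μg/g. It ranges from no loss, for raw ANCOVA with many readings at the ceiling, to about two thirds, for raw ANOVA without a ceiling at log-SD 1.6. The scale dependence of an interaction test is plain algebra and applies only if such a test is used. This should be settled before unblinding. It does not affect the primary outcome.

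**What to change.** In Statistical analysis, add for FCAL:

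- Arms are compared on week-12 log FCAL, with log baseline FCAL as a covariate in every case.
- Results are reported as ratios of geometric means with 95% CI.
- Combination against placebo, combination against each single product, and any interaction used to support synergy are tested on that scale.
- Values below the LLOQ, and any above the upper limit, are treated as censored rather than as exact readings.

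If the unseen analysis plan already says this, a cross-reference is enough.

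The cost is a few sentences and no new data. Effects will be reported as percentage reductions instead of μg/g differences. If many readings sit at the ceiling, there is little or no power gain over raw ANCOVA; what remains is a fixed scale and guaranteed baseline adjustment.

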### Data management

After obtaining informed consent from participants, the collected data will be stored in secure electronic databases within the University of Wollongong network by the trial coordinator (DC), accessible only to the specified members of the research team. Once participants are enrolled in the study and assigned a participant ID, participant names will be de-identified from documents and replaced with participant ID. All data will be stored electronically for 15 years before destruction. The final trial dataset will only be accessible to the specified members of the research team. A data safety monitoring board will not be convened for this clinical trial due to the absence of significant risk associated with the interventions and the early stage of this clinical trial.^(68)^ The research team will meet fortnightly during the conduct of the trial to oversee data collection and storage procedures.

## Discussion

To our knowledge, the current trial will be the first to investigate the combined effect of an anthocyanin and a multi-strain probiotic as an adjuvant therapy in mild-to-moderate UC. The results of the analysis may provide insights into the relationship between reduction of intestinal inflammation and changes to the faecal microbiota, which thus far have been studied separately in clinical trials of adults living with UC. This data may contribute towards the pursuit of targeted and individualised microbial therapies for treatment of inflammation and dysbiosis in adults living with UC. The findings of this study will additionally expand the current knowledge on the role of anthocyanins and specific probiotic strains as anti-inflammatory therapies in UC and may contribute towards the development of adjuvant anti-inflammatory dietary therapies that improve clinical outcomes, increase the QOL, and alleviate the burden of this disease for people living with IBD.
